### Safety outcomes

At the end of this trial, participants will participate in a routine physical examination consists of breath rate, heart rate, temperature, blood pressure, weight, routine urine, routine blood test, liver, kidney function tests, and electrocardiogram.

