**Design:**

This is a randomized, double-blind, placebo-controlled pilot clinical trial. A total of 124 participants suffering from insomnia symptoms will be randomly assigned to the JTW or placebo group in an equal ratio. The participants will be asked to take JTW or placebo granules twice a day for 1 week. All data will be gathered at baseline and at the end of the drug intervention. The primary outcome measures will be the mean change in the Pittsburgh Sleep Quality Index (PSQI) from baseline to the end of the drug intervention. Secondary outcome measures will include the altered sleep parameters in polysomnography, ^1^H-magnetic resonance spectroscopy (^1^H-MRS) evaluation, the Disharmony of Heart and Kidney Scoring System score, and blood tests, including the levels of serum adenosine and melatonin. A laboratory test will be taken before and after treatment to assess the safety of JTW.

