##### Blood tests

Blood tests consists of the levels of adenosine (AD) and melatonin (N-acetyl-5- methoxytryptamine) in blood samples will be recorded at the baseline and the end of the drug intervention and will then be analyzed by the clinical lab.

Sleep homeostasis in adults is affected by the sleep-regulatory substances AD and melatonin [29, 30]. AD is a product of brain metabolism and is closely related to sleep parameters. A previous study [31] showed that AD levels were elevated as a consequence of sustained wakefulness. Melatonin is an endogenous hormone produced by the pineal gland and is released exclusively at night. Melatonin has been shown to synchronize the circadian rhythms, and improve the onset, duration, and quality of sleep. Takaesu et al. thought that reduced secretion of melatonin may be involved in the mechanism of insomnia [32].

In the present study, high-performance liquid chromatography (HPLC) will be developed to determine the levels of adenosine, and an enzyme-linked immunosorbent assay will be used to detect the concentration of melatonin.

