### Statistical analysis

We will use two-sided *p* values for the primary outcome and for all secondary outcomes and safety variables. For the primary outcome, we will use Fisher’s exact test to test the hypothesis at null: the treatment has the same efficacy as the placebo. For each secondary outcome, defined as the value difference between baseline and end-of-intervention, we will use the following tests: (1) t-test for the continuous PSG variables; Chi-square test for the categorical PSG variables; (2) t-test for the blood-level adenosine and melatonin; (3) t-test for the GABA/Cr ratio; and (4) Wilcoxon rank sum test for the Disharmony Score of Heart and Kidney. For safety evaluation of JTW, a two-sided t-test will be applied to each safety measurement after data normalization.

We define the analysis population as the enrolled participants who have successfully completed the trial. We will characterize the types of individuals who have missing data to better understand the nature the missing mechanisms. We will use statistical models to impute missing values if the assumption of missing at random is met. This can preserve and utilize the information of the non-missing values.

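### The safety panel is given an end-of-trial time point in the methods but two time points in the abstract, and the planned safety t-test states no use of baseline

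*Protocol article*

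**What the plan says.** Three places in the protocol article bear on this point.

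- **Safety outcomes** (methods): "At the end of this trial, participants will participate in a routine physical examination". The panel is listed as "breath rate, heart rate, temperature, blood pressure, weight, routine urine, routine blood test, liver, kidney function tests, and electrocardiogram". No baseline time point is named.
- **Abstract, Design**: "A laboratory test will be taken before and after treatment to assess the safety of JTW". The same paragraph says of the trial as a whole: "All data will be gathered at baseline and at the end of the drug intervention".
- **Statistical analysis**: "For safety evaluation of JTW, a two-sided t-test will be applied to each safety measurement after data normalization". The same paragraph treats efficacy differently: "For each secondary outcome, defined as the value difference between baseline and end-of-intervention".

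Two further places matter. The exclusion criteria bar abnormal liver and kidney function, which implies that these two tests are done before entry. Fig. 2 is the schedule of enrolment, treatment and assessments, and its content is not available here.

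**The concern.** Every efficacy measure in the methods carries both time points. Adenosine and melatonin, for example, "will be recorded at the baseline and the end of the drug intervention and will then be analyzed by the clinical lab", and the sleep index, polysomnography, spectroscopy and disharmony score are scheduled in the same way. Only the safety panel has the end alone, so the omission does not read as obvious shorthand. A site that follows the methods section could reasonably collect the panel once.

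The analysis text shows the same contrast: change from baseline for secondary outcomes, a plain test on each measurement for safety. Safety is one of the stated aims of the trial. If baseline values are not collected, or are collected and not used, two things are lost:

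- precision in the comparison between arms for continuous measures;
- the ability to say whether an abnormal result after one week is new in that participant or was there before treatment.

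**Working it through.** The plan gives no figure to reproduce here. The check is a comparison of texts, then a short calculation of what baseline values are worth.

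**Step 1. How many panel measures have a stated or implied baseline?** The Safety outcomes section lists 10 measures: breath rate, heart rate, temperature, blood pressure, weight, urine, blood, liver function, kidney function and electrocardiogram. The number left without a baseline depends on which text is allowed to govern.

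| Reading | Measures without a baseline |
|---|---|
| Safety outcomes section taken alone | 10 |
| Plus the liver and kidney tests implied by the exclusion criteria | 10 − 2 = 8 |
| Plus the abstract's safety laboratory tests (urine, blood, liver, kidney) | 10 − 4 = 6 |
| The abstract's general sentence on all data | 0 |

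The range from 0 to 10 shows that the text is unsettled. It does not show which row describes the conduct of the trial.

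**Step 2. What does the analysis sentence use?** It names each safety measurement, a two-sided t-test and a prior normalization that is not defined. It mentions neither a change score nor baseline adjustment. This is so in every row of the table.

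**Step 3. What would baseline adjustment gain?** Take a continuous measure with the same variance at both times and correlation r between baseline and end. The documents give no value for r, so a range of 0.5 to 0.8 is assumed. Relative to the t-test on end values, the error variance is about

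- 1 − r² when the end value is adjusted for baseline;
- 2(1 − r) when the change score is tested.

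| r (assumed) | Adjusted for baseline | Change score |
|---|---|---|
| 0.5 | 1 − 0.25 = 0.75 | 2 × 0.5 = 1.00 |
| 0.7 | 1 − 0.49 = 0.51 | 2 × 0.3 = 0.60 |
| 0.8 | 1 − 0.64 = 0.36 | 2 × 0.2 = 0.40 |

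At r = 0.7 the end-only test has about half the information of the adjusted one. The change score gains nothing at r = 0.5 and is less efficient than adjustment throughout the range, so adjustment is the better choice.

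**Step 4. Where the calculation stops.** The factor 1 − r² concerns continuous measures. It does not apply to urine or electrocardiogram findings recorded as normal or abnormal. For these the gain is of another kind: paired values allow a count of participants who moved from normal to abnormal, and an end value alone does not.

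**The case against.** A reader might infer that most safety measures in this trial have no baseline. The documents do not support that. The Safety outcomes section does not say that the panel is done only at the end, and its sentence could simply describe the final visit. The abstract is part of the same article and says that all data are gathered at both times. The exclusion criteria imply pre-treatment liver and kidney tests. The figure that sets out the schedule is not shown, and it may list the whole panel at baseline. This part of the objection stands: absence of a baseline is not proven.

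It can also be said that, under 1:1 randomisation, a t-test on end values is a valid comparison between arms, that shift tables are often left to the analysis plan, and that the undefined normalization might involve baseline. The first of these stands, so the lack of adjustment is a loss of efficiency and not an error. The other two carry less weight. The protocol does fix a method for safety, and the sentence that fixes it says nothing about baseline, whereas the sentence on secondary outcomes in the same paragraph does.

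Finally, adverse events are recorded by daily telephone calls, so safety does not rest on the panel alone. That is correct, but calls do not detect silent laboratory or electrocardiogram changes.

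**Conclusion.** The concern holds in a limited form. The Safety outcomes section and the abstract give different timing for the safety assessments and must be reconciled against Fig. 2. Whichever schedule proves right, the stated safety analysis makes no use of baseline. The planned t-test remains valid between arms, but it is less precise than it could be and cannot separate new from pre-existing abnormalities in an individual.

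For continuous measures the loss is an error variance of 1/0.75 = 1.33 to 1/0.36 = 2.78 times that of an adjusted analysis. This rests on an assumed r of 0.5 to 0.8 and equal variances at the two times. No such figure can be given for categorical findings. This is an inexpensive improvement to the plan. It is not a demonstrated failure to collect baseline safety data.

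**What to change.** 1. Check Fig. 2, then reword the Safety outcomes section in line with the abstract so that the full panel is stated at baseline and at the end of treatment.
2. In the Statistical analysis section, replace the safety t-test for continuous measures with a comparison of end values adjusted for the baseline value (analysis of covariance), and say what the normalization is or remove it.
3. For laboratory, urine and electrocardiogram results, add a table by arm of shifts from normal to abnormal.
4. For participants already enrolled, use the baseline or screening values that were collected, and report for each measure how many participants have one.

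If Fig. 2 already shows the panel at baseline, the cost is wording and a small amount of programming. If it does not, the added cost is the missing baseline measurements in participants still to be recruited. The article is based on a protocol version dated February 2020 and expects recruitment to run to December 2020, so the change can still be of use.

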### Reporting and treating of adverse events

During the treatment period, the researchers will record any adverse events (AEs) that will be defined as unpredictable, undesirable symptoms, signs, or diseases related to the treatment during daily telephone calls. The researchers will then comprehensively evaluate the correlation between these AEs and the experimental drugs according to the recorded details about AEs, including the manifestation, occurrence time, duration, cause, and treatment measures. Simultaneously, if any AE occurs, the investigator will take proper measures such as dose adjustment, drug withdrawal, and symptomatic treatment to ensure the safety of participants; all details will be written down carefully. Furthermore, continuous follow-up will be insisted upon until the condition of the participants returns to normal. Furthermore, an insurance contract will be concluded to cover financial compensation to participants who might be injured during the study.

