## Background

Sleep is essential to human health, but unfortunately, nearly one-third to one-quarter of the population in resource-poor countries suffer from insomnia at some level [1, 2]. With the increasing incidence of insomnia, there are different degrees of depression, anxiety, and other psychological diseases, which seriously affect the quality of a person’s daily life [3]. Psychological and behavioral therapy, Western medicinal therapy, and traditional medicinal therapy are the main treatments for insomnia [4]. Many clinical studies have supported the first two treatments; however, some risks of adverse reactions and tolerance have been reported. In addition, dependence and addiction seriously impact clinical efficacy. For instance, the long-term use of zolpidem, which is relatively safe and frequently prescribed for the treatment of transient insomnia, will increase the risk of dementia [5]. Thus, interest in using traditional medicinal therapies is increasing, especially in traditional herbal medicine [6].

The superiority and soul of traditional East Asian medicine is the system called “pattern identification,” which is used to diagnose and treat diseases based on the symptoms and the signs observed in patients. According to this system, insomnia has many different patterns, but disharmony of the heart and kidney is the dominant pattern [7, 8]. Moreover, Jiao-tai-wan (JTW) has been commonly used for the management of insomnia with a disharmony of heart and kidney pattern for centuries in China, Korea, and Japan [9].

In a review article by Yeung et al. [10], JTW was listed as one of the 10 most frequently examined standardized traditional herbal formulas for insomnia. A clinical study conducted in China showed that administration of JTW for 60 consecutive days could improve the Pittsburgh Sleep Quality Index (PSQI) [11]. Lu et al. [12] reported a significant decrease in scores in the Disharmony of Heart and Kidney Scoring System. Another study [13] demonstrated the effects of JTW in detail by alleviating the symptoms of palpitation and dizziness caused by the disharmony of the heart and kidney.

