### Participant drop-outs

The participant can decide to discontinue treatment at any time for any reason.The patient is non-compliant.The patients experiences a serious AE.

Drop-outs and withdrawals from the trial will be recorded throughout the intervention and follow-up periods. Their data will be collected in the case report form but will not be used for the final statistical analysis.

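### The adverse-event window and telephone route are not aligned with the end-of-trial safety examination, so individual abnormalities found there are not clearly counted as AEs

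*Protocol article*

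**What the plan says.** Four parts of the protocol article bear on this point.

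- **Reporting and treating of adverse events** sets the window: "During the treatment period, the researchers will record any adverse events (AEs"). The same sentence gives the definition and the route; AEs are "defined as unpredictable, undesirable symptoms, signs, or diseases related to the treatment during daily telephone calls". Two later sentences carry no time limit: "if any AE occurs, the investigator will take proper measures", and "continuous follow-up will be insisted upon until the condition of the participants returns to normal".
- **Safety outcomes** sets the timing of the examination: "At the end of this trial, participants will participate in a routine physical examination". It lists ten items: breath rate, heart rate, temperature, blood pressure, weight, urine, blood count, liver tests, kidney tests and ECG. The Intervention section agrees on timing, since participants attend when medication ends and are then examined. The Abstract adds: "A laboratory test will be taken before and after treatment to assess the safety of JTW".
- **Statistical analysis** gives one method for these items, a two-sided t-test on each safety measurement after normalization. The analysis population is participants who completed the trial.
- **Participant drop-outs** refers to a further period: "Drop-outs and withdrawals from the trial will be recorded throughout the intervention and follow-up periods". No other section says what that period is or whether AEs are recorded in it.

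**The concern.** Safety is one of the trial's stated aims. The article names a closing point and a means of capture for AEs, and neither plainly covers its own main source of objective safety information. A raised liver test or a new ECG change is not something a participant reports by telephone, and at this examination it comes to light when treatment is already over. The end-of-trial assessments also include polysomnography with an adaptation night, spectroscopy and blood sampling, and an event during these sits at or beyond the edge of the window.

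At stake is whether individual abnormalities are counted. If site staff apply the sentence literally, such findings enter only a comparison of means. If they apply it loosely, the findings enter the AE count. Two readers could produce different AE tables from the same records.

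**Working it through.** The article states no figure on this point, so the check is mainly a comparison of sections.

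**1. Window against examination.** AE recording is placed in the treatment period, which is one week. The examination follows the end of medication (Intervention) and is set at the end of the trial (Safety outcomes). All ten items are therefore obtained at or after the close of the stated window.

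**2. Route against examination.** The stated route is a daily call. None of the laboratory or ECG items can be obtained that way. No section says that examination findings are a second route into AE recording.

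**3. Whether such a finding could be new.** The exclusion criteria bar abnormal liver and kidney function at entry, and the Abstract promises laboratory tests before treatment. An abnormal liver or kidney result at the end would thus normally have arisen since entry, which is the kind of result an AE count is meant to show.

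**4. Whether the t-test does the same job.** Suppose one participant in an arm of n lies d standard deviations above the rest.

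- Shift in that arm's mean: d/n standard deviations.
- Standard error of the difference between arms: √(2/n) standard deviations.
- Ratio of shift to standard error: (d/n)/√(2/n) = d/√(2n).

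The inputs for n are 62 per arm randomized and 49 per arm before the drop-out allowance (Sample size). The values of d, 5 and 10, are my assumption and serve only as illustration.

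| d | n = 62, √124 = 11.14 | n = 49, √98 = 9.90 |
|---|---|---|
| 5 | 0.45 | 0.51 |
| 10 | 0.90 | 1.01 |

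Two participants in the same arm at d = 5 give the same ratios as one at d = 10. All are well below the 1.96 needed for two-sided significance at 5%. The calculation holds the standard deviation fixed; an outlier also inflates the estimated standard deviation, which lowers the ratio further. One or two marked individual abnormalities can therefore leave the t-test unremarkable.

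**5. Follow-up periods.** The drop-out section speaks of intervention and follow-up periods, while the AE section names only the treatment period. Whether anything is recorded about AEs in the second period cannot be told from the text.

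**The case against.** The strongest reply is that the article states when and how AEs are recorded without saying that nothing else counts. The definition includes signs, and a raised blood pressure, a fever or an ECG change is a sign on an ordinary reading. An abnormality found when medication ends may well have begun during treatment, so detection at the boundary is not the same as onset after it. The results are listed as safety outcomes and tested. Detailed rules for classing laboratory values are often left to a full protocol.

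Much of this stands, and it rules out several stronger readings that a reader might infer:

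- **That abnormal results at the examination trigger no follow-up.** The sentences on action and on follow-up until recovery apply to any AE, have no end date and are not tied to the telephone calls. Nothing says that an examination finding goes unfollowed.
- **That the reported AE rate will omit every laboratory and ECG abnormality, or that the data are lost.** The measurements are collected and analysed, and investigators may class a finding as a sign. Applying an assumed abnormality rate to 62 participants would give the chance that an abnormality occurs, not the chance that it is missed.
- **That the trial ignores rebound on stopping, a risk its own rationale relies on.** The Background says that "dependence and addiction seriously impact clinical efficacy", but about existing treatments, with long-term zolpidem as its example. It does not mention rebound and attributes none to a week of JTW. The Discussion already lists the short study and follow-up as limitations. Calls after the last dose would be a design preference.

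The reply does not remove the mismatch. The article does not merely leave the window open for another document; it states a window and a route that do not fit its own examination. The t-tests do not replace a count of affected individuals.

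**Conclusion.** The point holds as a failure to align stated rules. AE recording is set to the treatment period and to telephone calls, while the objective safety examination falls at or after the end of medication and is otherwise analysed only by comparing means. New individual laboratory, vital-sign or ECG abnormalities, and events during the end-of-trial assessments, are not clearly part of the AE count.

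All ten listed safety measurements are affected. The number of participants concerned cannot be derived, because the documents give no rate of abnormal results and no way to know how site staff would read the sentence. The conclusion rests on the wording as published and on the examination taking place once medication has ended, as the Intervention section says. It does not require that any result goes uncollected or unfollowed.

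**What to change.** - In Reporting and treating of adverse events, run AE recording from the first dose until the end-of-trial examination is complete and its results have been received. Name the examination and the end-of-trial assessments as routes of capture beside the daily calls.
- State there that a clinically significant new or worsened laboratory, vital-sign or ECG finding at the examination is recorded as an AE. The existing provisions on AEs then apply without change.
- In Statistical analysis, report these findings as counts of participants by arm, alongside the t-tests.
- Reconcile the AE window with the follow-up periods in Participant drop-outs: either say what those periods are and whether AEs are recorded in them, or remove the reference if no such period exists.

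The cost is a change of wording and one CRF line for examination-detected events. No extra visit, call or test is needed. The reported AE rate may rise slightly, because findings already collected would be counted.

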**Discussion:**

The outcomes of this study will confirm the efficacy of JTW for the treatment of insomnia symptoms and will also be used to monitor the safety of JTW.

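### The adverse event definition presupposes causality, and the drop-out and completer rules remove participants with serious adverse events from the safety analysis

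*Protocol article*

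**What the plan says.** Four places in the protocol article bear on this.

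- **Reporting and treating of adverse events.** Staff are to record any AE during the treatment period, by daily telephone call. AEs are defined as "unpredictable, undesirable symptoms, signs, or diseases related to the treatment". The section continues: "The researchers will then comprehensively evaluate the correlation between these AEs and the experimental drugs", using recorded details that include manifestation, timing, duration and cause.
- **Participant drop-outs.** The listed reasons include "The patients experiences a serious AE". Of drop-outs and withdrawals it says: "Their data will be collected in the case report form but will not be used for the final statistical analysis".
- **Statistical analysis.** "We define the analysis population as the enrolled participants who have successfully completed the trial". No other population is named for safety. The safety method is that "a two-sided t-test will be applied to each safety measurement after data normalization".
- **Safety outcomes.** The end-of-trial examination covers vital signs, weight, blood, liver and kidney tests, and also routine urine and an electrocardiogram.

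Safety is one of the aims in the Background, and the Abstract says that the outcomes "will also be used to monitor the safety of JTW".

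**The concern.** There are two main defects and one lesser one.

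First, the AE definition is circular. An event must be related to treatment, and unpredictable, to be an AE, yet relatedness is what researchers are to assess afterwards. A caller who follows the definition literally may leave out a known effect of the herbs or an event that seems to have another cause. An event that is never written down cannot be recovered by any later analysis plan.

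Second, the population rules select on the outcome of interest. A serious AE makes the participant a drop-out, and being a drop-out removes the participant from the analysis. The participants who carry the most information about harm are the ones taken out, and more are taken out of whichever arm does more harm.

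The lesser point is that one test of means is prescribed for all safety measurements, although some of them are not continuous.

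At stake is the safety conclusion, in a trial whose Discussion expects the results to guide prescribing.

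**Working it through.** **1. The AE definition against the causality step.** The order in the AE section is: record AEs, where an AE is by definition related to treatment; then evaluate the relation of these AEs to the drug. If the definition is applied at entry, the evaluation can only confirm what was already decided. If the evaluation is meant to be real, events of unknown relation must enter first, and the definition is wrong. Both cannot hold. Reading the term for unpredictable loosely, as untoward, does not help, because the relatedness condition remains.

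**2. The chain of exclusions.**
- Serious AE → listed drop-out reason (Participant drop-outs).
- Drop-out → data kept in the case report form but not in the final statistical analysis (same section).
- Analysis population → completers only (Statistical analysis).
- Exception for safety → none in either section.

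So a participant who drops out because of a serious AE is not in the analysed safety data. The reach may be wider: the AE section names drug withdrawal among possible responses to any AE, and the exclusion covers withdrawals as well as drop-outs. Whether stopping the drug counts as withdrawal from the trial is not stated.

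**3. How many participants could be missing.** The protocol gives no safety figure. Its sample size section gives 49 evaluable per arm and 20% drop-out: 49 / (1 − 0.2) = 61.25, rounded up to 62 per arm, 124 in total. The 49 is reproduced by the standard two-proportion formula for 70% versus 40%, two-sided 5%, 80% power, with continuity correction. The plan therefore allows for 62 − 49 = 13 participants per arm outside the analysis, for all reasons together.

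**4. Illustration of the bias.** The serious AE counts are assumed; the documents give none. Suppose k of 62 JTW participants have a serious AE, all become drop-outs, and no one else does. Intervals are exact (Clopper-Pearson) 95%. With zero events the upper limit is 1 − 0.025^(1/n).

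| k | All 62 | 95% CI | Completers | Upper limit |
|---|---|---|---|---|
| 1 | 1.6% | 0.04 to 8.7% | 0/61 | 5.9% |
| 3 | 4.8% | 1.0 to 13.5% | 0/59 | 6.1% |
| 5 | 8.1% | 2.7 to 17.8% | 0/57 | 6.3% |
| 6 | 9.7% | 3.6 to 19.9% | 0/56 | 6.4% |

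For k = 5 or 6 the observed rate in all participants lies above the upper limit from the completer analysis. With k = 6 and no events in 62 placebo participants, Fisher's exact test gives p = 0.028 on everyone; among completers there is nothing to compare.

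**5. The t-test.** The Statistical analysis section separates continuous from categorical polysomnography variables and assigns the latter a chi-square test. It makes no such split for safety, although routine urine and ECG findings are largely categorical. Normalizing such data does not make a comparison of means suitable.

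**The case against.** The strongest reply is that the protocol does not lose these data. The AE section says that any AE is recorded, asks for careful documentation and follows participants until they return to normal; the drop-out section keeps the data in the case report form. The exclusion is from the statistical analysis, not from reporting. This stands, and it limits the point in several ways.

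- A reader might infer that the trial would report no serious AEs whatever happened. The documents do not support that: a listing of serious AEs by arm remains possible.
- A reader might infer that AEs will certainly be under-counted. The instruction to record any AE and the later causality step both suggest that staff may record events of uncertain relation. Under-counting is a risk created by the definition, not an established result.
- A reader might object that no comparison of AE incidence is planned. That is silence in a journal article, and an analysis plan could fill it.
- A reader might add that a t-test cannot see harm in a few people. The arithmetic is easy: 2 of 62 participants raised by 3 SD move the arm mean by 2/62 × 3 = 0.097 SD, for which power at 62 per arm is about 8%. In simulations, 5% of participants shifted by 4 SD was detected in about 14% of trials, 8% shifted by 4 SD in about 28%, and 5% shifted by 8 SD in about 23%. All these inputs are assumed, so this shows a limitation of means but not an error in the plan.

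The planned imputation under missing at random does not rescue the exclusion. It does not return drop-outs to the analysis population, and absence because of a serious AE is tied to the harm being measured.

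What the reply leaves untouched is the written definition and the written exclusions without a safety exception.

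**Conclusion.** The point holds for two written rules. The AE definition contradicts the causality step that follows it and, read literally, can filter out expected or apparently unrelated events. The drop-out and completer rules remove from the safety analysis those who drop out because of a serious AE, which biases the analysed results toward no harm.

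The size of the bias depends on the number of such drop-outs, which is unknown. If every participant with a serious AE is handled as the drop-out list implies, the analysed count is zero in both arms; the table above shows the effect for assumed counts of 1 to 6. The claim that the trial cannot support any safety conclusion would go too far, because the excluded data are retained and can be listed.

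The t-test on categorical urine and ECG findings is a genuine but minor defect. The definition and the exclusions should be corrected before the safety data are analysed.

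**What to change.** 1. Define an AE as any untoward occurrence after first intake, whether or not expected and whether or not thought related. Record causality as a separate attribute of each event, judged by blinded staff.
2. State that the drop-out and completer exclusions do not apply to safety. Define the safety set as everyone who took at least one dose, analysed as treated, and give AE and serious AE counts by arm.
3. Compare categorical urine and ECG results as proportions abnormal. Keep the t-test for continuous measurements only.

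No participants are added and no rule on treatment or withdrawal changes. The cost is wording, an instruction for the case report form and the telephone calls, more recorded AEs, and a few extra tables.

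Timing matters for the first item. By the protocol's own dates, recruitment ran from September 2018 to December 2020 and this version is from February 2020. The safety set can be applied to everyone, since drop-out data are kept, but a new AE definition helps only from the day it is used. The report should say which participants were followed under which definition.
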